## Abstract

**Background:**

There has been controversy over the extent to which technology use in general—and social media exposure specifically—may be associated with adverse youth mental health outcomes. To date, studies have generally been small and exploratory, relying on youth self-reports to characterize technology and social media use patterns. The goal of this study is to explore the associations between objectively collected data, gathered through a commercially available app, and youth mental health outcomes.

**Objective:**

The broad goal of this study is to characterize the association between objectively measured technology/social media use and a range of mental health–related outcomes. Three specific aims will be initially addressed. First, we aim to quantify the association between objectively measured smartphone use and measures of well-being. Second, we aim to differentiate types of engagement—specifically, the types of content consumed versus the overall time spent on the device—and examine their association with outcomes. Third, we aim to identify moderating factors, such as age, gender, and socioeconomic status, that might influence these relationships. A secondary broad objective of this research is to establish a freely available data resource that can be accessed by qualified investigators to address a much wider range of questions in the future.

**Methods:**

Up to 1000 male, female, and nonbinary youth aged 8-17 years (inclusive), along with their primary caregivers, will be enrolled in the study. Youth participants must have their own dedicated iOS- or Android-based smartphone or tablet, and both they and their parents must be willing and able to download and install the data collection app on their devices. The study is open to all US-based participants who meet these 2 criteria. Following electronic consent (eConsent), participants and their caregivers will complete a range of baseline measures electronically, including assessments of psychiatric and social functioning, as well as measures of loneliness, digital stress, and disordered eating. Caregivers will be asked to provide information on the participant’s health and mental health history. Youth and caregivers will then complete a similar battery of assessments 1, 2, and 3 months after baseline. Youth participants will also respond to daily questions about their mood, stress, physical activity, and sleep. Both youth and their caregivers will be compensated for completing measures at each time point. The data collection app gathers a wide range of daily data from the participant’s device, including temporal patterns of use, the number and frequency of various app usage, social interactions within apps, and keystroke data. A variety of analytic methods will be used to address key questions related to how technology and social media use are associated with mental health and wellness outcomes.

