#### Digital Activity Data Collection

The Aura product (current version 3.34.2) is a consumer-focused digital security app available to any smartphone user with iOS (Apple Inc) or Android (Google LLC) operating systems. When activated as part of the Family Plan subscription (used in this study), the app continuously monitors and collects data on a child’s smartphone or tablet device usage. The data gathered include, but are not limited to, the following: time spent on the device; specific app usage patterns (including which app, total time, time of day used, etc); contact information (individuals with whom the child interacts through a range of apps and messaging platforms); content consumption (viewing history, search history, etc); and keystroke data (including overall sentiment).

As product updates and releases occur throughout the study, participants and their parents/caregivers will continue participation using the latest version operating on their devices. The commercially available version of the app is used for all data collection in this study, with no modifications. The app’s Privacy Policy and Terms of Service are included in Multimedia Appendix 3.

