### Statistical Considerations

#### Specific Aims

Three specific aims will be initially addressed in this work (Textbox 1).

Specific aims.Quantify the associationDetermine the strength and direction of associations between objectively measured smartphone use (eg, total screen time, frequency of use, specific app engagement) and self-reported well-being measures (eg, Kiddie Computerized Adaptive Testing [K-CAT], World Health Organization-5 Well-being Index [WHO-5]).Differentiate engagement typesEvaluate whether distinct aspects of smartphone engagement—specifically, the types of content consumed versus overall time spent on the device—show differential associations with well-being outcomes.Identify moderating factorsInvestigate the extent to which key person-centered characteristics, including age, gender identity, and socioeconomic status, moderate the relationships observed between smartphone usage and well-being.

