#### Statistical Analysis: Specific Objectives

##### Elastic Net Regression Modeling

We will employ penalized regression models to predict baseline self-report outcomes for well-being and mental health. Specifically, for each of the following outcome measures—the World Health Organization-5 Well-being Index (WHO-5) total score, the EPOCH Measure of Adolescent Well-Being total score, the K-CAT Depression Scale total score, and the UCLA Loneliness Scale total score—we will train an Elastic Net regression model using device usage features as predictors. To identify statistically significant predictors for each outcome, we will examine the coefficient estimates of the final trained model. Features with nonzero coefficients after Elastic Net regularization will be considered important predictors and explored further in post hoc analyses.

This approach will enable us to identify which specific aspects of smartphone usage are most strongly and statistically significantly associated with self-reported measures of well-being and mental health at baseline, directly addressing specific aim 1. Furthermore, by examining the patterns of significant predictors across the different outcome variables, we can gain insights into whether time- or content-based engagement metrics are differentially associated with well-being, contributing to specific aim 2. Additionally, by including potential moderators, we can begin to address specific aim 3.

The Elastic Net is a linear regression model that combines the penalties of both Lasso (L1) and Ridge (L2) methods. This approach is especially well-suited for data sets with many potentially correlated predictors, as it simultaneously performs variable selection—shrinking coefficients of irrelevant predictors to zero—and manages multicollinearity.

We consider an initial set of 21 features derived from device usage within the first 2 weeks of the study, proximate to the baseline outcome measures. Given the richness of the device usage data, there is no clear upper limit to the number of features that could be developed. However, 21 features were selected based on initial interest, divided between time-on-device metrics and content-specific engagement, in line with specific aim 2. Additional features such as age, gender identity, household income, and racial and ethnic background will be included to address specific aim 3.

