Despite the potential strengths of this research, there are limitations that need to be considered. First, the requirement that youth participants own their own devices may limit the representativeness and generalizability of the sample. This concern is somewhat mitigated by reports indicating that the majority of children aged 11 years and older own a phone, with ownership rates increasing through the teen years and over time [3,39,40]. A second limitation that may affect the generalizability of the findings is that children’s device usage could change as a result of app installation. For instance, parents may choose to implement time limits or content filters, which could restrict the applicability of the results to youth who use their devices without such restrictions. Additionally, given the remote nature of the study, we are unable to verify whether the device on which the app is installed for data collection is, in fact, the child’s primary device. We ask parents and children to attest to this during the consent/assent process; however, we do not independently verify it. As such, this may also affect the generalizability or reliability of the findings. Finally, it should be noted that all authors of this protocol are full-time employees of the study sponsor, Aura, and no independent researchers were involved in the development or implementation of the study. Other tools are available for researchers to gather similar device usage data from youth smartphone or tablet activity—for example, the Effortless Assessment Research System (EARS) [41]—which has been used in previous studies [42,43].

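### Aims 1 and 3 concern smartphone use, but tablets are enrolled too, and neither device type nor operating system is among the listed model terms, so age moderation could partly reflect device type

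*Protocol article*

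**What the plan says.** **Exposure named in the aims.** Specific Aims (Textbox 1) sets Aim 1 as the strength and direction of "associations between objectively measured smartphone use (eg, total screen time, frequency of use, specific app engagement" and similar measures. Aim 3 asks how far age, gender identity and socioeconomic status "moderate the relationships observed between smartphone usage and well-being". The abstract's Objective and the Introduction also name smartphone use for Aim 1.

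**Devices enrolled and measured.** The abstract's Methods state that "Youth participants must have their own dedicated iOS- or Android-based smartphone or tablet". Under Digital Activity Data Collection, "the app continuously monitors and collects data on a child’s smartphone or tablet device usage". The eligibility list under Participants asks only for a mobile device. Analysis Populations requires baseline assessments and at least 10 of 14 days of usage data, and does not restrict the primary population to phones.

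**Model terms.** Elastic Net Regression Modeling lists 21 usage features, 11 time-based and 10 content-based. It then says: "Additional features such as age, gender identity, household income, and racial and ethnic background will be included to address specific aim 3". These terms and their interactions enter the model as the test of moderation.

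**Age and phones.** The limitations, under Anticipated Findings, cite reports that "the majority of children aged 11 years and older own a phone", with ownership rising through the teens. Enrolment starts at age 8.

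**The concern.** Number and length of breaks, session length, late-night use and messages sent may not carry the same meaning on a phone that is carried all day as on a tablet that stays at home. A model that pools the two describes a mixture, whereas Aims 1 and 3 are worded for one component of it.

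Aim 3 is the more exposed. Age is a named moderator, and device type is plausibly related to age. If the association between recorded use and well-being differs by device type, and tablets are more frequent at younger ages, the age interaction picks up some of that difference. A reader would then be told that younger and older children respond differently to smartphone use, when part of the contrast is between tablets and phones. A larger sample makes such a finding more likely to be declared, not less.

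**Working it through.** **1. Passages side by side.**

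| Item | Where | Device wording |
|---|---|---|
| Aims 1 and 3 | Specific Aims | smartphone |
| Eligibility | Abstract, Methods | smartphone or tablet, iOS or Android |
| Data capture | Digital Activity Data Collection | smartphone or tablet |
| Primary population | Analysis Populations | no device restriction |
| 21 features (11 + 10) | Elastic Net Regression Modeling | none is device type or operating system |
| Added terms | Elastic Net Regression Modeling | age, gender identity, income, race and ethnicity; open list |
| Named subgroups | Analysis Populations | neither is named |
| Limitations | Anticipated Findings | device class not mentioned |

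**2. The plan's own figure.** Sample Size gives 160 participants for 80% power with 21 predictors and f² = 0.15. Take the overall F test with df1 = k, df2 = N − k − 1, noncentrality f²·N and alpha 0.05 (alpha is my assumption; it is not stated). With k = 21, N = 160 and power is 0.802, so the figure reproduces and is not in dispute. It serves here to price the extra terms, with f² held at 0.15:

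- Device type added, k = 22: N = 163.
- Device type and operating system added, k = 23: N = 166.
- Device type, operating system and 21 device-type-by-usage interactions, k = 21 + 2 + 21 = 44: N = 223.

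All are far below the target of 1000.

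**3. Whether the mechanism can work.** The documents give no tablet share and no device-type effect, so every input here is an assumption:

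- Age is uniform over 8 to 17, standardised as (age − 12.5)/2.87.
- Tablet share falls linearly from 70% at age 8 to 10% at age 17.
- Recorded use is 0.5 SD lower on tablets and rises by 0.3 SD per SD of age.
- Outcome residual SD is 1.
- The usage slope is −0.3 on phones and −0.3 + g on tablets, with no true age moderation.

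If device type is omitted, the average slope at a given age is −0.3 + g × (tablet share at that age). The share changes by −0.6/9 × 2.87 = −0.191 per SD of age, so the spurious usage-by-age coefficient is about −0.191g. That is −0.029 for g = 0.15 and −0.057 for g = 0.30. Simulated means were −0.030 to −0.032 and −0.063 to −0.066, close to this approximation, which ignores the dependence of use on device type.

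Share of 1000 ordinary least squares runs with the usage-by-age term nominally significant:

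| g | N | Device type omitted | Device type and its interaction included |
|---|---|---|---|
| 0 | 160 | 4.4% | 4.2% |
| 0.15 | 160 | 7.4% | 6.2% |
| 0.30 | 160 | 15.5% | 4.6% |
| 0 | 1000 | 4.7% | 5.1% |
| 0.15 | 1000 | 16.1% | 4.5% |
| 0.30 | 1000 | 54.9% | 5.8% |

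**4. The usage term itself (Aim 1).** Under the same device shares, suppose there is no true usage association and device type shifts the outcome by 0.2 to 0.4 SD. With device type omitted, the usage term is falsely significant in 6.4% to 9.0% of runs at N = 160 and 8.5% to 22.2% at N = 1000. With device type included, the range is 4.7% to 6.6%. Monte Carlo standard error near 5% is √(0.05 × 0.95/1000) = 0.7 percentage points.

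**The case against.** The protocol does not hide the mix. Tablets are stated openly, and the analysis sections mostly speak of device usage, so smartphone in the aims may be loose shorthand. The list of added terms is open, and a condensed article need not name every covariate. This stands in part: device type is not among the listed terms, which is different from being ruled out. It does not remove the mismatch between the aims and the devices enrolled.

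The link between age and tablets is inferred. The limitations cite population phone ownership, whereas children without their own device cannot enrol, so the tablet share among enrolled younger children is unknown. This stands; the link is plausible, not shown.

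The simulation uses assumed inputs and significance in ordinary regression, whereas the plan reads nonzero elastic net coefficients. This also stands: the percentages show direction and mechanism, and do not forecast the error rate of this study.

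Three stronger readings are tempting and are not supported:

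- **That the plan claims smartphone effects.** The aims speak of associations.
- **That a gap in recorded use measures the bias.** If tablets recorded half of identical behaviour, and tablet shares were 50% in younger and 5% in older children, mean recorded use would be 0.75 against 0.975 of true, a gap of about 23%. With shares of 20% and 5% it is 0.90 against 0.975, about 8%. These are gaps in mean recorded use under invented inputs. They are not biased coefficients, and a gap in mean use is not in itself an interaction.
- **That app updates bias the results.** The protocol says "participants and their parents/caregivers will continue participation using the latest version operating on their devices", but nothing in it suggests that capture differs between versions.

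**Conclusion.** The point holds as a mismatch that can be corrected cheaply, with a possible and unquantified consequence. Followed as written, the plan would draw smartphone and age-moderation conclusions from phones and tablets that the listed terms do not separate.

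Distortion of Aim 3 requires two things: tablet share must vary with age in the enrolled sample, and recorded use or its slope must differ by device type given the other terms. The protocol gives figures for neither. If there is no device-type effect, there is no bias, and the simulated error stays near 5%. If there is one, enrolling 1000 children makes the false age finding more frequent. The mismatch between aims and eligibility stands without any simulation.

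**What to change.** 1. Record the child's device type and operating system for the 2-week usage window. Both are simple to note at app set-up.
2. Include both as unpenalised adjustment terms in the elastic net models, so that the penalty cannot drop them. When age moderation is tested, add the device-type-by-usage interaction.
3. Restate the aims and conclusions as smartphone or tablet use.
4. Report a smartphone-only sensitivity analysis to support any statement specific to smartphones. It need not replace the pooled analysis; making it the main analysis would be a debatable trade-off.
5. App version need not be a model term.

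The cost is two recorded items, a few more model terms and one extra model run, with fewer children in the sensitivity analysis. The Results section places the initial analysis in late autumn 2025 or winter 2026, so at the time of writing the change could still be made before any model was fitted. Because the data are to be shared, recording device type also serves later investigators.

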**Results:**

Enrollment for this study began on November 13, 2024. As of May 20, 2025, a total of 106 participants and their caregivers had consented to participate and provided baseline data. An additional 203 children and parents have consented and are currently undergoing eligibility verification and enrollment. Initial data analysis is anticipated to begin in late autumn 2025 or winter 2026, with the expected publication of initial findings in spring 2026.

**Conclusions:**

This study will be among the largest to date to collect both objective device usage data and validated, clinically relevant outcome measures. In accordance with our data-sharing policies, any qualified investigator will be able to access the study data, provided appropriate steps are followed.

**Trial Registration:**

ClinicalTrials.gov NCT06664944; https://clinicaltrials.gov/ct2/show/NCT06664944

**International Registered Report Identifier (IRRID):**

DERR1-10.2196/69358

## Introduction

Over the past 15 years, there has been a dramatic rise in technology use among children and adolescents, particularly following the introduction of smartphones [1]. Nearly 95% of adolescents report using social media [2]. By age 17, the vast majority of youth in the United States have access to a smartphone and report spending hours on it daily. Nearly 50% say they are on social media and other smartphone-based apps “nearly constantly” [3].

Concurrent with these changing patterns of technology use by young people, there has been widespread concern about increases in youth mental health problems, including self-harm/self-injurious behavior, rates of mood and anxiety problems, and self-reported loneliness. Even in the decade preceding the onset of the COVID-19 pandemic, high school students reported increases in feelings of sadness and hopelessness, along with higher rates of suicidal ideation and behavior [4]. Since 2020, there is considerable evidence that rates of mental health challenges among youth, such as depressive and anxiety symptoms and self-harm, have continued to rise. The scope of these challenges prompted both the US Surgeon General and the American Academies of Pediatrics and Child and Adolescent Psychiatry to issue proclamations calling for a range of measures to address the problems [5,6]. Yet, more than 3 years later, there is little evidence that rates of mental health challenges among youth are abating.

Given the temporal congruence between the rise of technology and social media use and the reported increases in youth mental health challenges, much research and public discussion have centered on how these trends may be related. The link between social media use in particular and adverse mental health outcomes has drawn national attention, including a US Congressional hearing with the chief executive officers of the top social media companies [7], and 2 additional reports from the US Surgeon General specifically highlighting potential harms of social media use on youth mental health [8,9]. Most recently, the Governor of California signed a bill banning social media apps from sending notifications during school hours and late at night, and is considering a bill that would require a mental health warning label on social media apps [10].

Despite the highly publicized concern over the link between tech/social media use and mental health outcomes in young people, the published evidence is mixed. Many studies report associations between social media use and mental health problems [11-13], while others find weak or no relationship—or even a positive link [14-16]. One reason for these mixed findings is almost certainly that the relationship between smartphone use and mental health outcomes is not straightforward. A myriad of person-centered factors (eg, age, sex/gender identity, preexisting mental health condition, reward sensitivity), content exposure (eg, inappropriate material, cyberbullying), and nondevice activities (eg, in-person connection, physical activity) can influence the links between smartphone use and mental health outcomes [17,18].

One common feature of studies examining the mental health impacts of smartphone or social media use on young people is the nature of data collection. The literature in this area typically relies on self-reports of usage patterns by youth themselves or their caregivers [19]. However, the correlation between self-reported social media use and objectively derived use (from the devices themselves) is modest. For example, a meta-analysis of 47 studies found a correlation of 0.35 between self-reported and objectively measured social media use [20]. Given the limitations of data collection in previous studies, there is general agreement—both in the published literature and in reports from the Surgeon General and other public sources—on the need for more objective data to better understand how technology and social media use may influence mental health outcomes in young people.

The overall goal of this longitudinal, observational study is to examine the association between youth technology and social media use and mental health outcomes, including mental health and wellness, physical activity, digital stress, and loneliness, as well as daily ratings of mood, stress, and sleep. Our initial analysis, described in this protocol, will focus on 3 primary aims. First, we aim to quantify the association between objectively measured smartphone use and measures of well-being. Second, we aim to differentiate types of engagement—specifically, the types of content consumed versus the overall time spent on the device—and their associations with outcomes. Third, we aim to identify moderating factors, such as age, gender, and socioeconomic status, that might influence these relationships.

A second broad goal of this research is to establish a data set that can be used by a wide range of investigators to address a variety of questions over time. The specific aims outlined above represent our initial priorities for data analysis, but our study design will support the exploration of a myriad of additional questions.

This research will extend previous work in 3 important ways. First, device usage data will be collected using a commercially available product (the Aura app), which provides an objective measurement of a wide range of youth digital activity, including patterns of time spent on various apps throughout the day and overnight, social interactions, messages sent across platforms, and derived sentiment from outgoing messages. Second, rather than examining the relationship between device usage and mental health outcomes solely at the population level, we will leverage the unique combination of objective smartphone data and daily subjective well-being measures to adopt an idiographic approach. This allows us to use individuals as their own baselines, capturing within-person changes in smartphone use to predict corresponding shifts in well-being over time. Third, the granularity of the data will allow us to identify distinct usage patterns across children and adolescents. By including person-centered factors (eg, age, gender, and race/ethnicity) alongside both device usage and off-device behaviors, the data could help uncover protective and moderating effects within broader behavioral trends. These refined approaches—leveraging both the depth and breadth of objective and subjective data on smartphone use and well-being—aim to clarify this controversial topic and provide a foundation for a wide range of subsequent research, clinical interventions, and policy development.

